## Abstract

The number of individuals with age-related cognitive impairment is rising dramatically in the UK and globally. There is considerable interest in the general hypothesis that improving the diet of older people may slow the progression of cognitive decline. To date, there has been little attention given to the possible protective role of n-3 long-chain polyunsaturated fatty acids (n-3 LCPs) most commonly found in oily fish, in age-related loss of cognitive function. The main research hypothesis of this study is that an increased dietary intake of n-3 LCPs will have a positive effect on cognitive performance in older people in the UK.

To test this hypothesis, a double-blind randomised placebo-controlled trial will be carried out among adults aged 70–79 years in which the intervention arm will receive daily capsules containing n-3 LCP (0.5 g/day docosahexaenoic acid and 0.2 g/day eicosapentaenoic acid) while the placebo arm will receive daily capsules containing olive oil. The main outcome variable assessed at 24 months will be cognitive performance and a second major outcome variable will be retinal function. Retinal function tests are included as the retina is a specifically differentiated neural tissue and therefore represents an accessible window into the functioning of the brain.

The overall purpose of this public-health research is to help define a simple and effective dietary intervention aimed at maintaining cognitive and retinal function in later life. This will be the first trial of its kind aiming to slow the decline of cognitive and retinal function in older people by increasing daily dietary intake of n-3 LCPs. The link between cognitive ability, visual function and quality of life among older people suggests that this novel line of research may have considerable public health importance.

## Background and rationale

The number of individuals with age-related cognitive impairment is rising dramatically in the UK [1] and globally [2]. Global burden of disease estimates now place dementia above stroke, musculoskeletal disorders, cardiovascular disease and all forms of cancer in terms of the percentage of years lived with disability in people aged 60 years and older [2]. Defining simple and effective strategies to prevent or delay cognitive impairment among older people is therefore a priority for healthcare and social services.

There has been specific interest in the hypothesis that enhancing the diet of older people may act to slow the progression of cognitive decline. The importance of good nutrition among older people for the maintenance of health has long been advocated, and evidence-based dietary recommendations for older people have been published [3]. However, for a variety of functional, physiological, psychological and social reasons older people are nutritionally vulnerable, and frequently consume diets that are poor in both quality and quantity resulting in macronutrient and micronutrient under-nutrition.

Interest has recently turned to the potential importance of n-3 long-chain polyunsaturated fatty acids (n-3 LCPs), largely obtained from oily fish, in the maintenance of good cognitive health. The brain is particularly rich in the n-3 LCP docosahexaenoic acid (DHA), and n-3 LCPs have repeatedly been shown to be crucial to brain development in humans [4]. Age-related decrease in n-3 LCP level in total brain lipids have been reported in humans, and it has been postulated that this decline is correlated in part with age-related deterioration of functions of the central nervous system [5,6]. This findings may be particularly relevant in the UK since recent survey data [7] demonstrates that older people in the UK habitually consume a diet that is low in fish.

A recent cross-sectional survey has reported that higher fatty fish and n-3 LCP consumption is associated with reduced risk of cognitive impairment [8], and prospective studies have demonstrated that increased fish consumption is associated with decreased risk of dementia [9,10] and Alzheimer's disease [11] among older people. Data from a cohort study recently suggested that reported daily use of fish-oil supplements was associated with improved scores in cognitive function at age 64 years, even after correcting for childhood cognitive ability [12].

Numerous randomised controlled trials have demonstrated that a relative sufficiency of n-3 LCPs results in improved sensitivity to light in infancy [4]. It is thought that this results from the ability of n-3 LCPs (specifically DHA) in rod outer segments of the retina, to enhance photoreceptor signal transduction processing. Relative inadequacy of DHA results in decreased signal transduction, and DHA deficient subjects therefore require greater light stimulation to elicit the same level of photoelectric response. In addition DHA plays a key role in photoreceptor growth and functional development, a role which has recently been demonstrated to be mediated by DHA effects on gene expression [13].

A highly significant change occurring in the ageing retina is a decrease in phototransduction efficiency in rods resulting in a decreased sensitivity of rods to light [14]. Part of this decreased sensitivity may be associated with reduction in DHA levels, such as also occurs in the ageing brain, and may be susceptible to dietary manipulation. It is hypothesised that increasing dietary DHA intake among older people will result in increased levels of DHA in the brain and retina, and therefore enhance phototransduction efficiency and consequently light sensitivity.

A recent Cochrane review [15] concluded that there was a growing body of evidence from biological, observational and epidemiological studies that suggested a protective effect of n-3 LCPs against dementia. However, the Cochrane review team was unable to locate a single published randomised controlled trial on which to base recommendations for the use of dietary or supplemental n-3 LCPs for the prevention of cognitive impairment or dementia. The current study will be the first trial of its kind aiming to slow the decline of cognitive and retinal function in older people by increasing daily dietary intake of n-3 LCPs. The link between cognitive ability, visual function and quality of life among older people suggests that this novel line of research may have considerable public health importance. Furthermore, improving the quality of life and independence of older people, may help to reduce the number of disability-adjusted life-years lost through poor cognitive and retinal function in the UK.

## Design and methodology

### Design

The study is designed as a double-blind randomised placebo-controlled trial. The procedures are illustrated schematically in Figures 1 and 2, and detailed in the text. The trial aims to test two primary hypotheses.

**Figure 1 F1:**
[figure not shown]
Flow-chart of cognitive function study protocol.

**Figure 2 F2:**
[figure not shown]
Flow-chart of retinal function study protocol.

### Study hypotheses

**Cognitive function study **– for healthy, cognitively normal adults aged 70–79 years of age, daily supplementation with n-3 LCPs (500 mg DHA and 200 mg EPA) will slow the rate of cognitive decline.

**Retinal function study **– for healthy, cognitively normal adults aged 70–79 years of age, daily supplementation with n-3 LCPs (500 mg DHA and 200 mg EPA) will improve visual function by enhancing rod photoreceptor response to light and visual-cortical integration.

### Inclusion criteria

#### (i) Centres

20 National Health Service general practices, members of the Medical Research Council General Practice Research Framework (GPRF) will be recruited. The retinal function sub-study practices will be situated in the Southeast of England to facilitate attendance at Moorfields Hospital.

#### (ii) Patients

Participating general practices, will draw a sample of healthy, cognitively-normal adults aged 70–79 years from their practice registers. These potential participants will be pre-screened for eligibility, by study nurses employed by each practice, using available clinic records and a GPRF computer identifier programme. Individuals currently diagnosed with either diabetes (Type I or Type II) or dementia will be excluded. The exclusion of individuals with diabetes is necessary as these individual will have raised susceptibility to vascular and neural damage and may therefore be less sensitive to the proposed intervention. Individuals with pre-diagnosed dementia will be excluded as the intervention is aimed at delaying cognitive decline in people who are currently not demented. The list of potential participants will be checked by the named General Practitioner in the clinic who will use discretion to exclude individuals not deemed suitable to take part in the study (e.g. recent bereavement, terminal illness).

Eligible individuals identified by this process will each receive a letter and information sheet from their general practice outlining the nature and importance of the study. The letter will also act as a screen for potential participants who are currently consuming fish-oil supplements. Participants reporting the current daily use of fish-oil supplements will be excluded from the trial. Potential participants will be invited to make an appointment with the research nurse at their local general practice. Participants will be offered the use of a taxi, or their travel costs on public transport or mileage in private cars to attend the appointment up to a maximum of £10. The invitation letter will explicitly state that if they do not wish to take part in the study, it will not prejudice the quality of health care provision from their general practice.

On attending their general practice, potential participants will be fully informed by the research nurse about the nature and relevance of the trial, and exactly what will be involved if they agree to take part. All potential participants will be told that a prerequisite of their joining the study will be that they agree not to initiate non-study fish-oil supplement use over the course of the trial. Potential participants who remain interested in taking part in the study, will then be asked to give consent to undergo a short cognitive screen, the Mini Mental State Examination (MMSE). The MMSE is an easy to administer test that has been widely validated as a screen for dementia and will be used to exclude participants with low cognitive status [16]. Participants with an MMSE score of less than 24 (out of a maximum of 30) will not be included in the trial, and will be offered a referral to their General Practitioner for further monitoring. The cut-off of less than 24 has traditionally been used as a marker for possible dementia in adults. It is possible that individuals with an MMSE of 24 or greater may have mild dementia. However, given the potential public health relevance of this trial, the purpose of the proposed cut-off is to exclude individuals with possible frank dementia rather than select a highly functioning group of individuals. Individuals with an MMSE score below 24 will be thanked for their time and co-operation.

Participants who score MMSE of 24 or greater will be invited to give full, informed written consent to take part in the main cognitive function study. Individuals unwilling to participate further will be thanked for their time and co-operation.

Individuals giving informed consent will be enrolled in the trial. The research nurse will telephone the central randomisation service to register the participant, giving identifying details and the participant's age. Randomisation will allow secure blind allocation of eligible people to one or other arm of the study. Following random allocation a study number will be given for each study participant. This will also be used to identify the supply of capsules to be prescribed for each participant. The study number will be entered on the participant's entry form. Pre-labelled identical-looking packs of capsules (see *Dietary Intervention *below) will be stored securely in the general practice. Minimisation criteria will be used to ensure a balance of key prognostic factors using the following two criteria: age group (70–74 and 75–79 years) and general practice.

Participants will then be assessed by completing questionnaires and undertaking a series of tests (see *Baseline Data Collection *below). The full set of baseline tests will take approximately 60 minutes to complete. Any couples recruited to the study will undertake their assessments separately. Participants will be provided with the contact details of the study nurses and trial manager. Information will also be available from the trial web-site [17] for those participants who wish to use this method of obtaining information. Participants will be thanked for their time and co-operation.

## Cognitive function study

### Outcome measures for cognitive function study

#### Primary outcome

Change in cognitive function at 24 months determined by the California Verbal Learning Test. This is a test of memory of 16 words.

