### Sample size

The sample size required for this trial is based on a 0.3SD difference between trial arms in long-delay free recall of List A of the California Verbal Learning Test over the 24 months of intervention. To detect a 0.3SD difference between trial arms, with 90% power and 1% significance, 332 individuals are required per treatment group. Allowing for 20% drop-out over 24 months of intervention, the total sample size required for the study is 798 individuals. A difference of 0.3SD is clinically relevant and would be equivalent to individuals in the intervention arm being able to remember one more word out of the 16 in the California Verbal Learning Test than those in the placebo arm [18].

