8. Fish consumption: two simple questions regarding habitual fish consumption will be asked. Firstly, a question regarding the frequency of fish consumption, and second, participants will be asked to list the three species of fish they consume most frequently.

9. Cognitive ability: the participants will be asked to complete a validated series of cognitive tests. It is currently not known which, if any, cognitive domain will be most affected by n-3 LCP supplementation and therefore a series of tests have been selected which cover the major domains (memory, attention, psychomotor speed and executive function):

a. Brief assessment of subjective symptoms of cognitive impairment (memory, language/word-finding, concentration).

b. Immediate and delayed recall of a short story (from the Wechsler Memory Scale).

c. Immediate and delayed recall of a 16-item word list (California Verbal Learning Test).

d. Three tests of prospective memory i.e. remembering to carry out instructions without being reminded.

e. Timed letter search/cancellation task (attention/psychomotor speed/executive function).

f. Verbal fluency – naming animals (word-finding/executive function).

g. Digit span forwards and backwards (working memory/executive function) from the Wechsler Adult Intelligence Scale.

h. Symbol digit modalities test (attention/psychomotor speed/executive function).

i. Simple (psychomotor speed) and choice (decision speed) reaction time.

j. Spatial memory (memory/visual spatial function).

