### Data analysis for assessing change in cognitive function

Primary analysis will be carried out based upon the groups as randomised ("intention to treat"). Results will be presented as appropriate effects sizes with a measure of precision (95% confidence intervals). Covariates such age, gender, and baseline blood pressure and DHA concentration will be adjusted for in the analysis. Further exploratory analyses will be based on those patients who fully follow the treatment protocol.

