## Retinal function study

### Outcome measures for retinal function study

#### Primary outcome

Change in rod sensitivity over 24 months of intervention as measured by electroretinogram.

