### Data analysis for assessing change in retinal function

Primary analysis will be carried out based upon the groups as randomised ("intention to treat"). We will test between group differences in change in rod sensitivity over the 24-month follow-up. We will carry out secondary outcome analysis on change in colour vision based on colour contrast specificity. Covariates such as age, gender, and baseline blood pressure and DHA concentration will be adjusted for in the analysis. Results will be presented as appropriate effects sizes with a measure of precision (95% confidence intervals). Further exploratory analyses will be based on patients fully following the treatment protocol.

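### Both primary outcomes are change from baseline, but the named covariates omit the outcome's own baseline value; naming it gains precision at no cost

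*Protocol article*

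**What the plan says.** The cognitive primary outcome is "Change in cognitive function at 24 months determined by the California Verbal Learning Test" (Cognitive function study, Primary outcome). The sample size section narrows this to "long-delay free recall of List A of the California Verbal Learning Test over the 24 months of intervention". The retinal primary outcome is "Change in rod sensitivity over 24 months of intervention as measured by electroretinogram" (Retinal function study, Primary outcome).

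The cognitive analysis section names no model or test. On adjustment it says: "Covariates such age, gender, and baseline blood pressure and DHA concentration will be adjusted for in the analysis". The retinal analysis section is more definite: "We will test between group differences in change in rod sensitivity over the 24-month follow-up". It then says: "Covariates such as age, gender, and baseline blood pressure and DHA concentration will be adjusted for in the analysis". The baseline value of the primary outcome appears in neither list.

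Both baseline values are collected. The word-list test is item 9c of the baseline cognitive battery, and the full electroretinogram is item 1 of the baseline retinal data. Allocation is minimised on age group and general practice only.

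The cognitive sample size reads: "To detect a 0.3SD difference between trial arms, with 90% power and 1% significance, 332 individuals are required per treatment group". The same section equates 0.3SD with one extra word of the 16. The retinal section sets the effect at 1SD, with 90% power and 5% significance, and arrives at 22 per group. Neither section says whether its SD is that of a single reading or of the change, and no correlation between baseline and 24 months is given.

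**The concern.** For a repeated memory score or a repeated electroretinogram, the baseline value of the same measure would usually be the strongest predictor of the 24-month value. The protocol names four covariates and leaves that one out, while framing the outcome as change. Subtracting the baseline in full is not the same as adjusting for it. Unless r is 1, subtraction over-corrects: an arm that starts higher by chance tends to show a smaller gain, and the estimated effect shifts the opposite way. Nothing in the minimisation guards against such an imbalance, and the retinal sub-study has only 22 per group.

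What is at stake is precision in both studies and, under one reading of the effect sizes, whether the stated power is reached.

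**Working it through.** **Inputs.** Cognitive: 0.3SD, 1% significance, 90% power, 332 per arm. Retinal: 1SD, 5%, 90%, 22 per arm (the two Sample size sections). The correlation r is not given, so it is an assumption shown over a range. Baseline and 24-month variances are taken as equal and set to 1.

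**Reproducing the stated figures.** The two-sample formula is n = 2(z_alpha/2 + z_power)^2 / d^2, with two-sided tests.
- Cognitive: 2(2.576 + 1.282)^2 / 0.3^2 gives 331, against 332 stated. Power at 332 is 90.1%.
- Retinal: 2(1.960 + 1.282)^2 / 1^2 gives 22, as stated. Power at 22 is 91.3% by the normal approximation and 90.0% by noncentral t.

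Both plans therefore come from a formula with SD = 1 and no correlation term.

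**Variances.**
- Change score without baseline adjustment: SD = sqrt(2(1 - r)).
- Analysis adjusted for baseline: residual SD = sqrt(1 - r^2).
- Ratio of variances: 2(1 - r)/(1 - r^2) = 2/(1 + r), which exceeds 1 for every r below 1.

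**Power if 0.3SD and 1SD are SDs of a single score.** Normal approximation, 332 and 22 per arm, other covariates ignored in both analyses:

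| r | SD of change | SD adjusted | Variance ratio | Cognitive: change / adjusted | Retinal: change / adjusted |
|---|---|---|---|---|---|
| 0.3 | 1.183 | 0.954 | 1.54 | 75.5% / 93.0% | 80.0% / 93.5% |
| 0.4 | 1.095 | 0.917 | 1.43 | 83.0% / 95.0% | 85.7% / 95.1% |
| 0.5 | 1.000 | 0.866 | 1.33 | 90.1% / 97.0% | 91.3% / 96.9% |
| 0.6 | 0.894 | 0.800 | 1.25 | 96.0% / 98.8% | 96.0% / 98.6% |
| 0.7 | 0.775 | 0.714 | 1.18 | 99.2% / 99.8% | 99.0% / 99.6% |

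The threshold follows directly: the SD of change is no larger than the planning SD when 2(1 - r) <= 1, that is r >= 0.5. At r = 0.4 the cognitive study would need 397 per arm with unadjusted change and 278 with adjustment.

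**Power if they are SDs of change.** The planning SD is then already the right one for a change score. Power at 332 is 90% at any r, and adjustment still multiplies the variance by (1 + r)/2.

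**Which SD?** One word for 0.3SD implies an SD of 1/0.3 = 3.3 words. That reads more naturally as the spread of a score, but the text does not say so. The retinal section gives no comparable clue.

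**Chance imbalance.** A baseline difference of D shifts the expected change-score difference by -(1 - r)D. The standard error of a baseline difference is sqrt(2/22) = 0.30SD in the retinal study and sqrt(2/332) = 0.08SD in the cognitive study. At r = 0.5, an imbalance of one standard error shifts the estimate by 0.15SD and 0.04SD respectively. Averaged over randomisations the shift is zero.

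**The case against.** The strongest reply is that the protocol does not exclude the baseline value. Both covariate lists are introduced as examples, so they are open. The cognitive section names no model at all. Defining an outcome as change does not rule out baseline adjustment either: regressing change on treatment and baseline gives the same treatment estimate and standard error as regressing the 24-month score on them. The full model may sit in a plan that is not shown. All of this stands. A reader might infer that the trial is committed to comparing raw change. The documents do not support that, since both sections promise covariate adjustment and only the retinal section states a test of change.

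A reader might also infer that the 90% power rests on a correlation of 0.5 or more. That holds only if the effect sizes are in SDs of a single score. The cognitive section ties its difference to the 24 months of intervention, so an SD of change is a fair reading, and the dependence then disappears.

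A third inference, that the change score is biased, is too strong: under randomisation it is unbiased on average, and the shift is conditional on a chance imbalance.

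Finally, the gain may be modest. At r of 0.6 or more, power at the stated numbers is at least 96% either way under the single-score reading, and the document gives no reason to expect a lower r.

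What remains is that the article does name covariates, omits the baseline of the outcome, and would do better to include it whatever r below 1 proves to be.

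**Conclusion.** The point holds as a free improvement in precision, not as a demonstrated loss of power. Without baseline adjustment, a change analysis has 2/(1+r) times the variance of the adjusted one, or 1.18 to 1.43 times for r between 0.7 and 0.4. This assumes equal variances at the two times. The estimate would also move with any chance baseline imbalance, most noticeably in the retinal sub-study.

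The power consequence is conditional. With single-score SDs and no baseline adjustment, the stated 332 and 22 per arm deliver about 90% only from r of about 0.5 upward. With SDs of change there is no shortfall. The protocol does not settle which applies. These figures use the stated evaluable numbers and leave aside how drop-out was allowed for, which is a separate matter.

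**What to change.** In each of the two data analysis sections, add one sentence naming the baseline value of the primary outcome as a covariate in the primary analysis: baseline List A long-delay free recall for the cognitive study, and baseline rod sensitivity for the retinal study. The outcome definitions can stay as change, because with that covariate included, change and the 24-month value give the same treatment effect.

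In each of the two sample size sections, state whether the SD is that of a single reading or of the 24-month change and, if it is that of a single reading, give the correlation assumed.

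The cost is a few sentences. The baseline measurements are already planned, and no further participants, visits or tests are needed.
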